# STUDY DESIGN

## STUDY CONFIGURATION

This is a pilot study, single centre, 14 day study comprising of (i) questionnaires of bowel habit, pain and anxiety, a bowel habit and pain 14 day diary, (ii) biological samples: 1 stool sample and 1 * 20ml blood sample and (iii) an MRI scan of the abdomen to identify fat distribution and large and small bowel water content.

# Methods

## Participant groups

We will recruit n = 35 participants in each group (Total 105). Participants will include;

- 1. 35 participants with symptomatic DD and a patient heath questionnaire 15 score of >7
  2. 35 participants with symptomatic DD and a patient heath questionnaire 15 score of <7
  3. 35 participants with asymptomatic DD

The DD groups will be age and sex matched.

Having excluded those with e.g severe co-morbidity, alcoholism or drug dependence or inability to give informed consent (see exclusion criteria), we will invite participation in the MRI study day.

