| Outcome measures | Primary End-point  1. Difference in the volume of visceral fat compared to abdominal subcutaneous fat between symptomatic and asymptomatic DD groups  Secondary End-Points. Differences between:   1. Adiponectin and leptin serum levels between symptomatic and asymptomatic DD groups 2. The incidence of diarrhoea between participants with a BMI <25Kgm-2 and those >25Kgm-2. 3. Adiponectin and leptin serum levels between DD groups with and without diarrhoea 4. Small and large bowel water and lumen diameter in symptomatic and asymptomatic DD groups 5. Calprotectin levels between symptomatic and asymptomatic DD groups. 6. Microbiological gut profile between symptomatic and asymptomatic DD groups. |
| Statistical methods | Statistical analysis will carried out with the use of Prism 4 (GraphPad Software Inc, San Diego, CA). Comparisons between groups were performed by using 2-tailed unpaired t test or the Mann–Whitney's U test, for normal and non-normal data respectively. |

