**Possible mechanisms linking obesity to symptomatic diverticular disease**

1. **Association with lifestyle risk factors**

It has been speculated that the increase in incidence of diverticular disease and its complications[3], may be linked to changing western lifestyle. Western diets, especially the lack of cellulose in the diet, and decreased mobility increase the risk of developing diverticular symptoms[20, 21]. As these are linked with the development of obesity, a high BMI may be a surrogate marker for other lifestyle factors that predispose to diverticular complications. Obesity has also been linked to other gastrointestinal pathologies[22-24], including colorectal carcinoma[24-26], chronic inflammation[25, 27] and changes in gastrointestinal microflora.

1. **Inflammation**

Visceral fat has secretes systemic factors that influences on metabolic, endocrine and immunological functions. Visceral fat can also have local influences upon the organs it surrounds, in a paracrine manner. Adipocytes secrete a variety of important compounds:

1. **Adipokines and cytokines**
   1. **Adiponectin**

Adiponectin is produced from adipocytes [28, 29]. Adiponectin is inversely related to BMI and its levels are greater in women than men[24]. Low adiponectin levels and higher concentrations of cytokines, e.g. TNF alpha, IL6, IL8, IL10 and IL1beta, are thought to be involved in the development of insulin resistance and possibly insulin growth factor(IGF) and IGF binding proteins 1 and 2[24].

Adiponectin also has anti-angiogenic and anti-inflammatory effects. Deficient mice have more severe form of chemically induced colitis that normal mice[30, 31]. Variations in adiponectin concentrations have also been reported in UC and Crohn’s disease (CD). Adiponectin and leptin have been shown to be up-regulated in CD compared to visceral fat samples from colon cancer or diverticular disease patients[32].

- 1. **Leptin**

Leptin is an adipocyte specific hormone. It acts on appetite and bodyweight and circulating levels have been associated with colonic cancer. It has similar effect on oesophageal and colonic cell lines, increasing angiogenesis, cell proliferation and metalloproteinase expression.

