Leptin levels correlate with white adipose fat mass and is coded for by the obese (ob) gene, while its receptor is coded by the diabetes (db) gene. Levels are greater in women than men, even when adjusted for by BMI. It has multiple actions in satiety and inflammation (see figures from Lago et al 2007[33]).

It acts on a variety of immunological cells such as monocytes, neutrophiles, basophils, NK cells and T cells. In T cells it effects the activation and balance between TH1 and TH2 cytokine production, causing a pro-inflammatory TH1 response. Leptin is itself increased by mediators of inflammation such as lipopolysaccharide (LPS), IL-1 and IL-6. Knockout mouse models suggest leptin is important in development of inflammatory diseases, such as colitis. However its exact mechanism is not fully understood[33].

Leptin has been identified as a critical component in the development of tactile allodynia in a partial sciatic nerve ligation (PSNL) mouse model of pain. After PSNL, adipocytes around the epineurioum increased expression of leptin. Mice given antibodies against leptin and leptin knockout mice failed to produce allodynia, which was reverse after administration of leptin. It is thought that leptin acts by attracting Macrophages, with leptin receptors to injured nerves and caused production of pro-nociceptive mediators Leptin induces iNOS, COX-2 and MMP-9 via phosphorylated signal transducers and activators of transcription 3 (pSTAT3) pathways, which up-regulate the expression of leptin[34]. Peritoneal administration of leptin has also been found to cause pain in mice models[35].

In clinical studies, individual levels of adipokines from synovial fluid, from arthritic knees undergoing joint replacements, did not correlate well with pain scores. However adioponectin-leptin ratios were significantly correlated with pain scores from the Short form McGillPain questionnaire[36]. Waist circumference, BMI and female sex have also been found to be predictive of leptin levels in synovial fluid[37]. Leptin has also been suggested to play a role in endometriosis patients with chronic pelvic pain[38]. From Lago et al 2007[33].

1. **Inflammatory cells**

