## SECONDARY OBJECTIVES

Differences between:

1. Adiponectin and leptin serum levels between symptomatic and asymptomatic DD groups
2. The incidence of diarrhoea between participants with a BMI <25Kgm-2 and those >25Kgm-2.
3. Adiponectin and leptin serum levels between DD groups with and without diarrhoea
4. Small and large bowel water and lumen diameter in symptomatic and asymptomatic DD groups
5. Calprotectin levels between symptomatic and asymptomatic DD groups.
6. Microbiological gut profile between symptomatic and asymptomatic DD groups.

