# STATISTICS

### Methods

Statistical analysis will carried out with the use of Prism 4 (GraphPad Software Inc, San Diego, CA). Comparisons between groups were performed by using 2-tailed unpaired *t* test or the Mann–Whitney's *U* test, for normal and non-normal data respectively by [name] and [name]

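### Groups are matched on age and sex but compared with unadjusted unpaired tests: precision is lost on the matched contrasts, and the adipokine comparison by diarrhoea status is unprotected against sex imbalance

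*Protocol*

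**What the plan says.** Under Participant groups the protocol sets up three groups: symptomatic with a PHQ-15 score above 7, symptomatic with a score below 7, and asymptomatic. The sizes are given as "We will recruit n = 35 participants in each group (Total 105"), followed by "The DD groups will be age and sex matched". It does not say whether matching is individual or by frequency, or how close it must be.

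The Synopsis (Statistical methods) fixes the analysis: "Comparisons between groups were performed by using 2-tailed unpaired t test or the Mann–Whitney's U test, for normal and non-normal data respectively". The Methods paragraph of the Statistics section repeats this ("Comparisons between groups were performed by using 2-tailed unpaired"). No pairing, stratification or covariate is mentioned anywhere.

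The primary objective contrasts symptomatic with asymptomatic disease. Secondary objective 3 uses another grouping: "Adiponectin and leptin serum levels between DD groups with and without diarrhoea". The background section says of adiponectin: "Adiponectin is inversely related to BMI and its levels are greater in women than men". Of leptin it says: "Levels are greater in women than men, even when adjusted for by BMI".

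**The concern.** Matching takes age and sex variation out of the difference between groups. An unpaired test leaves that variation in the standard error, so design and analysis do not fit together. Intervals for the symptomatic versus asymptomatic contrasts come out wider than the data warrant, and the benefit of matching is partly thrown away.

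For secondary objective 3 the problem runs the other way. Participants are sorted by diarrhoea status, for which nothing was matched, and the outcomes are two hormones that the protocol describes as higher in women. If the share of women differs between those with and without diarrhoea, a sex difference can be read as an adipokine difference, and the named tests cannot remove it.

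**Working it through.** **The plan's own figure.** The sample size section gives 35 per group for a 30% difference in visceral fat, 90% power and p<0.05, but no SD or CV, so 35 cannot be reproduced directly. Back-solving the two-sided t test at 35 per group gives a standardised difference d = 0.786, hence an implied CV of 0.30/0.786 = 38%. This d is used below as the planned effect.

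**Matched contrasts.** Let R2 be the share of outcome variance explained by age and sex. It is not in the protocol, so a range is assumed. With exactly matched groups:
- unpaired SE / true SE = 1/sqrt(1-R2)
- true two-sided type I error ≈ 2 × Φ(-1.96/sqrt(1-R2))

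| R2 (assumed) | SE ratio | True type I error |
|---|---|---|
| 0 | 1.00 | 5.0% |
| 0.1 | 1/sqrt(0.9) = 1.054 | 3.9% |
| 0.2 | 1/sqrt(0.8) = 1.118 | 2.8% |
| 0.4 | 1/sqrt(0.6) = 1.291 | 1.1% |

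Simulating the t test on exactly matched groups agrees: 3.8%, 2.9% and 1.3% at 35 v 35. The SE ratio does not depend on the allocation, so it also holds at 70 v 35.

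Power at d = 0.786. The unadjusted figures are simulated under matching. The adjusted figures come from the noncentral t distribution with effect d/sqrt(1-R2).

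| R2 | 35 v 35: unadjusted, adjusted | 70 v 35: unadjusted, adjusted |
|---|---|---|
| 0.1 | 91%, 93% | 97.0%, 97.7% |
| 0.2 | 92%, 95% | 97.8%, 98.8% |
| 0.4 | 95%, 99% | 98.8%, 99.8% |

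The 70 v 35 columns apply if the two symptomatic groups are pooled. The gain is about 2-4 points at 35 v 35 and about 1 point at 70 v 35.

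**Adipokines by diarrhoea status.** Let D be the sex difference in within-sex SD units, and p1 and p0 the shares of women with and without diarrhoea. If diarrhoea has no true effect:
- spurious difference b = D × (p1 - p0)
- SE = sqrt[(1 + D²p1(1-p1))/n1 + (1 + D²p0(1-p0))/n0]
- false-positive rate ≈ Φ(-1.96 + b/SE) + Φ(-1.96 - b/SE)

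D, p1 and p0 are assumptions. Two splits of the 105 were used: 26 v 79 (about a quarter with diarrhoea, assumed) and 13 v 92 (the background figure of 12.2% chronic diarrhoea; 0.122 × 105 = 12.8).

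Worked case: D = 1, p1 = 0.75, p0 = 0.50, 26 v 79. Then b = 0.25 and SE = sqrt(1.1875/26 + 1.25/79) = 0.248. The rate is Φ(-0.95) + Φ(-2.97) = 17%.

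| D | Women, with v without | 26 v 79: formula (simulated) | 13 v 92: formula (simulated) |
|---|---|---|---|
| 0.5 | 60% v 50% | 5.5% (5.5%) | 5.3% (5.3%) |
| 0.5 | 70% v 50% | 7.2% (6.9%) | 6.3% (6.0%) |
| 1.0 | 60% v 50% | 6.8% (6.5%) | 6.1% (6.1%) |
| 1.0 | 70% v 50% | 12.6% (12.1%) | 9.4% (9.0%) |
| 1.0 | 75% v 50% | 17.2% (16.5%) | 12.0% (11.3%) |

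If the share of women is equal in the two groups, b = 0 and the rate stays at 5%.

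**The case against.** **The primary analysis remains valid.** Its error is conservative, the bias reduction from matching is kept, and the study is labelled a pilot. This stands, and it is why the point is not graded as a must-fix.

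**The size is assumed.** The protocol gives no R2, and the endpoint sets visceral against subcutaneous fat, for which R2 may differ from that for visceral fat alone. At R2 = 0 nothing is lost, and matching looser than the exact balance assumed here shrinks the effect. This stands too: only the direction is firm.

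**Confounding by sex needs two links.** The protocol supports the link from sex to adipokines. It says nothing that links sex to diarrhoea. The imbalances above are therefore scenarios, and with a 10-point imbalance the false-positive rate is only about 5-7%. What remains is that the design does nothing to prevent an imbalance.

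**Covariates may be left to a later plan.** The abbreviations list mentions a Data Analysis Plan. But the protocol does not stay silent: it names the tests twice, so a later plan that followed it would carry the mismatch forward.

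**Stronger readings are tempting.** A reader might infer that adjustment lifts power from 90% to 95-99%. It does not: 90% is the power without matching, and the matched but unadjusted test already reaches about 92-95% at R2 of 0.2-0.4. A reader might also extend the point to secondary objective 2. That is an incidence of diarrhoea by BMI, so the sex difference in adipokines does not bear on it. Nor does naming a test for normal and another for non-normal data fix a faulty pre-testing procedure.

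**Conclusion.** The mismatch is in the protocol's own text, and the direction of both consequences follows from it.

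For the matched contrasts, the unadjusted interval is about 5%, 12% or 29% too wide at R2 of 0.1, 0.2 or 0.4, given close matching. That costs precision. It does not support a claim that the primary result would be biased or give too many false positives.

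For secondary objective 3, the unadjusted test is open to confounding by sex. The false-positive rate is about 7-17% at 26 v 79 or 6-11% at 13 v 92 if the sex gap is 0.5-1.0 SD and the shares of women differ by 20-25 points. A reader might take this as proof that the comparison is confounded; the documents show only that it is unprotected.

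Severity: should-fix.

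**What to change.** In the Synopsis (Statistical methods) and in the Methods paragraph of the Statistics section, replace the unadjusted tests for the continuous endpoints with a linear model containing group, age and sex. If matching is individual, the matched set can take the place of age and sex, so state under Participant groups which kind of matching is used. Transform skewed outcomes where suitable. For secondary objective 3, fit the same model with diarrhoea status in place of group. Keep the unpaired t and Mann-Whitney tests as a sensitivity check.

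The cost is wording. Date of birth is already recorded on the study forms, and sex must be known in order to match on it. No participants, visits or measurements are added. The authors should confirm that the named software fits the model, or name one that does.

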## MRI study day protocol

Participants will be required to make 1 visit to the department. Prior to the visit we will ask participants to complete a 14 day bowel habit diary sheet and provide a stool sample, to bring on the day of their MRI visit.

The participants will visit the ***Brain and Body Centre*** after a overnight fast (fast of 12 hrs food and 6 hr for clear fluids). They will be asked to omit any laxatives for 24hrs and antispasmodics for 12hrs prior to the MRI study day. The participants will be screened and consented for the MRI study. They will have baseline pulse, blood pressure, height and weight, waist and hip circumference measured and recorded and will complete a safety questionnaire to ensure there are no contraindications to MRI (i.e. have metal implants or pacemaker).

Participants will be shown the 1.5T MRI Philips Achieva scanner. They will be positioned supine in the scanner with a parallel imaging body coil wrapped around the abdomen. Several different imaging sequences will used to optimally image the different regions of the gut as follows;

1. SBWC will be assessed with a single shot, fast spin echo sequence. This scan will take approximately 10 minutes.
2. A dual-gradient echo imaging sequence will be used to visualize anatomy. This scan will take approximately 10 minutes.

Including set-up and imaging, the volunteers spend approximately 20 minutes inside the magnet.

## Biological samples

### Stool samples

Participants will be asked to freeze their stool samples in the domestic freezer prior to bringing it to the B&B centre. Pots, gloves, bags and detailed instructions will be provided to the participants to prevent contamination of food by faeculent material. Samples will be brought to the B&B centre by the participant and frozen at -20oC so that the sample time of >-20oC is kept to a minimum time of 1.5hrs. All samples will be anonymised and stored at -20oC in the Nottingham Digestive Disease Centre freezers. Samples will be analysed for calprotectin and genetic techniques (e.g. quantitative PCR or microarray) to identify diversity of gastrointestinal microflora between groups.

**Blood samples**

20ml of blood will be taken to assess plasma levels of;

Adipokines – adiponectin and leptin

Inflammatory mediators – e.g. TNF alpha, IL-6, IL-10, IL-8, IL-4, IL-1, CRP

Biochemical characteristics – insulin, fasting glucose, triglycerides, liver function tests

All samples will be anonymised and stored at -80oC in the Nottingham Digestive Disease Centre freezers.

## Data Analysis

The visceral and subcutaneous fat, and SBWC images will be analyzed with the use of in-house software as previously described and validated by intubation studies at 1.5T[48].

## STUDY MANAGEMENT

The study has been adopted by the Nottingham Digestive Disease Centre (NDDC). The CI will oversee the day to day running of the study. Study supplies will be purchased through the NDDC and shipped to the Brain and Body imaging centre, as required. [name] will be responsible for ordering supplies. [name] will be responsible for co-ordinating analysis of the MRI samples. [name] will be responsible for co-ordinating analysis of the questionnaires

The data will be collected from participants into individual participant folders. All study documents will be labelled with the participants study code. Files will be stored in a locked filing cabinet in a locked office in the NDDC on [name], Queen’s Medical Centre. [name] is the custodian of the study data.

## DURATION OF THE STUDY AND PARTICIPANT INVOLVEMENT

Participants will be required to make 1 visit to the department. Prior to the visit we will ask participants to complete a 14 day bowel habit diary sheet and provide a stool sample, to bring on the day of their MRI visit.

On the day of the visit they will be consented for the scanning part of the study, give a 20 ml blood sample and have a 20-25 minute MRI scan of their abdomen. The visit will last approximately 1 hour.

### End of the Study

The end of the study for the participant is on the MRI scanning day. No further follow up of the participant will be planned. If medical abnormalities are found in the data collected, the participants will be referred to appropriate NHS Heath care professions for continued investigation and treatment. The research team will not formally follow up any participant where a medical abnormality has been detected once appropriate NHS care has been organised.

## SELECTION AND WITHDRAWAL OF PARTICIPANTS

### Recruitment

## Participant Selection and Recruitment

Participants will be recruited from gastrointestinal medicine and surgery clinics and databases of patients with diverticular disease held at the NDDC, who have previously expressed interest and or have previously participated in research. The initial approach will be from a member of the participant’s usual care team or researcher. Information about the study will also be on display in the relevant clinical areas. Potential participants from clinics will be initially approached by a member of their usual care team, which may include the investigator, regarding the study. Participants will only be approached directly by the research team if they have been consented previously to being contacted for future research. NDDC databases will be reviewed by [name], [name] or [name] (NDDC Database Manager).

A newspapers advert may also be placed in local newspapers and associated news websites e.g. the Evening post, if required. Interested individuals who want more information about the study will be able to contact the research team using the telephone, email and postal address provided. An answer phone message for the study will be provided to allow messages to be recorded at any time. The research team to return calls to the advert-responders, briefly describe the study to the potential participant, check that they are suitable for the study using a structured proforma and answer any questions before sending out the patient information sheet, introduction letter and questionnaire.

The letters to potential participants contain a reply slip/questionnaire consent form and questionnaire, which they can return to give the research team permission to verify the diagnosis of diverticular disease by checking hospital records or contacting the potential participant’s GP. A Medical trained profession from the research team will review any hospital records in order to verify a diagnosis of diverticular disease. This may be required even for potential participants recruited through clinic as their normal care team may not be able to fully assess the potential participant for the inclusion and exclusion criteria.

The patient’s general practitioner may be contacted by post initially with a standardised letter, copy of the patient’s signed consent form to allow information to be given to the research team and a copy of the patient information leaflet. If no response is received within 2 weeks, a member of the research team will phone the GP practice to confirm they have received the original letter. If not, the letter will be sent again by post or secure fax to the GP practice to be completed by the GP. The completed form can be returned by post to the NDDC or by secure fax. If the completed form is not received with in following 2 weeks, the GP practice will be contacted again to identify any problems. If the GP practice fails to give out the requested information after this further contact, the potential study participant will be informed that without confirmation of their diagnosis of diverticular disease we are unable to include them in the study. If the potential study participant wants to contact their GP themselves directly, the research team will forward a copy of the GP letter with a free post envelope to him/her.

If the research team cannot confirm the diagnosis of diverticular disease from past radiological or endoscopic investigations, we will not recruit the potential participant to the study. All consent and procedures will occur at Nottingham University under [name] research team.

The investigator(s) from the research team or a member of the participant’s usual care team, will inform the participant or their nominated representative (other individual or other body with appropriate jurisdiction), of all aspects pertaining to participation in the study. Written information will be provided with an introductory letter, participant information leaflet, questionnaire, reply form and return envelope. If written information cannot be provided at the time of the clinic visit, verbal consent will be gained for the information to be posted to the participant’s home address.

The participants will have up to 2 weeks to decide. If they return the reply slip and/or questionnaire, they will be contacted by a member of the research team regarding a time to attend for the MRI visit or to discuss the study in more detail. This may be via telephone or post. The questionnaire will allow clarification of gastrointestinal specific inclusion and exclusion criteria. Other inclusion and exclusion criteria may be clarified by post, on the telephone or by using patient hospital records, with patient consent. This is to avoid unnecessary travel and inconvenience to the participant if this information has not been previously obtained or is ambiguous from the questionnaire.

